**Fig 3 pone.0351577.g003:**
[figure not shown]
Intramuscular (IM) and skin temperature responses to a 90‑minute local heat therapy session. **(A)** IM temperature was continuously monitored using an implanted thermocouple. Each unique symbol represents data recorded from a different participant. **(B)** The minimum (min; open circles) and maximum (max; filled circles) IM and skin temperatures recorded during a 90-minute local heat therapy session.

### At-home local heat therapy sessions

Participants are provided with their two heat pads with flannel inserts, four Velcro straps (two per leg), and a log to record details of each at-home local heat therapy session. Participants are instructed to empty their bladder before starting each session to minimize interruptions. Then, they securely place heating pads around each thigh, ensuring a snug fit with Velcro straps, and set them continuously at the predetermined temperature for 90 minutes. Participants record the start and end times for each session, the number of times the heating pads are removed, duration of and reason for each removal, and any discomfort experienced. There are no specific restrictions regarding session location (e.g., home or office), time of day, or permitted activities during the session (e.g., watching TV, reading). Participants are advised to set a timer or alarm and to remain awake during each session. Lastly, the number of at-home local heat therapy sessions completed each week will be recorded to evaluate adherence and compliance with the protocol.

To ensure safety during at-home heat therapy and to facilitate participant acclimation over the 12-week intervention period. For all at-home heat therapy sessions, participants will document the temperature used, the duration of heat exposure, and any pertinent notes (e.g., discomfort) allowing individualized monitoring of thermal exposure and acclimation and ensuring safe progression. These records will be reviewed to monitor adherence, track thermal acclimation, and ensure that progression remains within safe limits.

### In-laboratory local heat therapy sessions

Immediately on arrival for each weekly in-laboratory heating session, participants return their logs from the prior week’s at-home heating sessions to confirm compliance. Then, they void their bladder and anthropometric measures (body mass, waist circumference, and hip circumference) are obtained. Following anthropometric measurements, heating pads are applied to both legs and set to the pre-determined temperature for 90 minutes. During the 90-minute heat pad application, research staff monitor participants’ comfort level and skin temperature for both legs every 5 minutes and measure blood pressure every 10 minutes. During the 90-minute session, participants complete the Hooper questionnaire, IPAQ, TLFB, and ASA-24. At weeks 6 and 12 of Phase 1, the IM temperature measurement is repeated during the in-laboratory heat therapy session.

### Study monitoring

#### Evaluation of adverse events.

Local heat therapy may cause mild thermal discomfort, erythema, or, rarely, localized blistering following heat exposure, especially if used improperly or for prolonged periods. However, the risk of significant injury is low, as the heat pad applied to the thigh is unlikely to raise core body temperature. Skin and body temperature are monitored during lab sessions, and therapy will be stopped if body temperature exceeds 40°C. To ensure safety, the lowest effective heat setting is used, and participants are asked to set a timer to limit sessions to 90 minutes. Minor skin redness may occur but typically resolves within 12 hours. Any skin discomfort experienced during the heat pad sessions is documented during both in-laboratory and at-home use, and any discomfort reported during in-laboratory sessions is promptly addressed and used to inform adjustments for subsequent at-home sessions. Participants receive contact information for reporting any issues. Weekly in-lab sessions are supervised by the study team to ensure safety throughout the intervention.

In the event of mild adverse thermal reactions (e.g., erythema or blistering), participants will be instructed to apply aloe vera or fragrance-free moisturizer to the affected area. If the blister opens spontaneously, participants will be advised to apply a thin layer of antibiotic ointment to protect the exposed skin. Both in-laboratory and at-home heat therapy will be temporarily suspended for the affected limb. Adverse reactions will be monitored by the clinical research coordinator through follow-up communication and photographic documentation until complete resolution. Communications and photographs will be relayed to our safety officer (SO) and reported to appropriate parties in accordance with our Data and Safety Management Plan. The study team will follow any additional guidance provided by the SO.

#### Criteria for discontinuing.

Participants may be withdrawn from the study by the research team if necessary. Specifically, this may occur if a participant initiates a significant lifestyle change (e.g., starting a new exercise regimen, dietary program, or supplement routine) or develop a new health condition that may increase their risk. Additionally, participants who do not adhere to at least 80% of the study requirements may be subject to early discontinuation.

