## Abstract

**Introduction:**

Glycemic dysregulation is a hallmark of type 2 diabetes (T2D) and contributes to skeletal muscle (SKM) loss and frailty risk, especially in older adults. Glycemic control and physical function are supported by SKM capillarization and mitochondrial function, and their impairment contributes to T2D development. While high-intensity interval training (HIIT) is a promising intervention, adherence and effectiveness remain concerns for prescribing HIIT among older adults at risk for T2D. Local heat therapy (LHT) may be a more practical initial strategy to improve SKM architectural factors and precondition SKM, enhancing physiological adaptations to exercise in this population.

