### Power analysis

A power analysis was performed using G*Power (version 3.1.9.4). Because capillary-fiber perimeter exchange index (CFPE) is a widely measured variable and an important component of anticipated adaptations, we used the results from Kim et al.[27] to power this study. They observed significantly greater CFPE with LHT vs CON (d > 1.5). We used a more conservative, d = 1.2 (reduced by 20%), because older adults might have a blunted response to LHT. We used the statistical analysis of Aim 1 to power the study because it involves more groups (three) and thus requires the largest number of participants. The one-way ANOVA with three groups (d = 1.2, f = 0.4899, α = 0.05) will require 45 total participants (15 per group) to achieve 80% power. This will be followed by two non-orthogonal planned contrasts (CON vs. LHT, LHT vs. HIIT). These *t*-*t*ests (d = 1.2, α = 0.05/2 [Bonferroni]) also require 15 participants per group to achieve 80% power. In the statistical analysis of Aim 2, only two of the three groups are included, leading to greater statistical power. The planned *t*-*t*est (d = 1.2, a = 0.05, 15 participants per group) will achieve 89% power. If needed, the one-way ANOVA with two groups (d = 1.2, a = 0.05, 15 participants per group) will also achieve 89% power. Comparing this number of participants per group to previously published work examining LHT and SKM mitochondria, capillarization, and size [26–28], 15 participants per group is a comparable estimate of sample size. Although not identical to our proposed work, sample sizes of 10 (within-subjects) [23] and 18 (9 per group, between-subjects) [31] were sufficient to detect improvements in glycemic control in overweight men and in obese women with polycystic ovarian syndrome, respectively, in response to whole-body heat therapy. Our power analysis and previously published research support a target sample size of 15 participants per group (CON, HIIT, and LHT). Accounting for a potential 18% attrition rate, we aim to enroll 18 participants per group (9 men, 9 women) for a total target enrollment of 54 participants.

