Because the study utilizes balanced permuted block randomization, we expect key baseline characteristics, such as sex assigned at birth, age, and glucose tolerance, to be well-balanced across the three treatment groups. Our analysis will begin with a one-way ANOVA to evaluate primary treatment effects. To ensure the model is both parsimonious and robust, we will perform residual diagnostics by plotting residuals against various participant characteristics (demographic, clinical, and molecular). Non-random residual distributions will signal the need to include missing main effects, while diverging patterns across treatment levels will indicate potential interaction effects. These additional terms will be formally tested for significance before being integrated into the final model.

Note that integrating covariates into the model generally enhances the power to detect treatment effects by reducing error variance. Conversely, the power to detect interaction effects is usually low, as these effects typically exhibit smaller magnitudes and larger standard errors. Given that our sample size is determined based on a one-way ANOVA, all interaction analyses will be treated as exploratory.

While we anticipate complete data sets for primary outcomes assessed at T1, T2, and T3, there is a possibility of missing data. To address potential bias and maintain statistical power in the presence of potential missing data, we will employ Multiple Imputation by Chained Equations. We will generate several imputed datasets using all available baseline characteristics and previous timepoint values. Each dataset will be analyzed independently using the specified ANOVA or ANCOVA model, and the resulting estimates and standard errors will be pooled to produce a single inference according to Rubin’s Rules. This approach accounts for both within-imputation and between-imputation uncertainty.

To assess the robustness of our primary findings, a sensitivity analysis will be performed. While the primary analysis assumes data are Missing At Random, we will explore the impact of Missing Not At Random data. Specifically, we will apply a penalty to the imputed values of the treatment group to simulate a scenario where participants who dropped out had poorer outcomes than those who remained. If the treatment effect remains statistically significant under these conservative assumptions, the primary results will be considered robust.

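### The discontinuation rule does not keep withdrawn participants in outcome follow-up, so the primary estimates can drift toward an effect among adherers

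*Protocol article*

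**What the plan says.** The Criteria for discontinuing section opens with a general power: "Participants may be withdrawn from the study by the research team if necessary". It gives two kinds of ground. On behaviour, "this may occur if a participant initiates a significant lifestyle change", with a new exercise, diet or supplement programme as examples; a new health condition that may raise risk is listed beside it. The section then adds that "participants who do not adhere to at least 80% of the study requirements may be subject to early discontinuation". Nothing there says that a person who is withdrawn or discontinued is still invited to T2 or T3. The Retention section supports complete follow-up in general but does not exempt these people.

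On missing outcomes, the Statistical analyses section plans multiple imputation by chained equations: "We will generate several imputed datasets using all available baseline characteristics and previous timepoint values". The assumption is explicit: "While the primary analysis assumes data are Missing At Random". For a departure from it, "we will apply a penalty to the imputed values of the treatment group".

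The Blinding and unblinding section says that staff are told whether a participant is in HIIT or a heat-pad group. Those caring for heat-pad participants adjust the settings and communicate the target temperature. The Abstract gives as part of the rationale that "adherence and effectiveness remain concerns for prescribing HIIT among older adults at risk for T2D".

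**The concern.** Adherence and lifestyle change arise after randomisation and can depend on the assigned arm. If they end outcome collection, the people measured at T2 and T3 are a selected part of those randomised. The power to withdraw is discretionary. The article does not reserve the decision for someone blinded, and the staff closest to the participant know HIIT versus heat pad and can know the heat setting.

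Both aims are exposed:

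- **Aim 1** compares the effectiveness of LHT with HIIT, and low exercise adherence is one reason for the trial. An estimate that leans on adherers takes part of that difference out of the comparison.
- **Aim 2** compares LHT with CON after both do HIIT. The Introduction expects prior heat therapy to help later exercise adherence, so withdrawing poor HIIT adherers in Phase 2 would select on something that LHT is expected to change.

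A biopsy or glucose tolerance test that was never done cannot be recovered later by an analysis plan.

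**Working it through.** **1. The plan's own figures.** Power analysis uses d = 1.2. With three groups, f = 1.2 × √(1/6) = 0.4899, as stated. For 45 participants the ANOVA power is 81.7%. A contrast at two-sided alpha 0.025 with 15 per group has 81.5%. The stated 15 per group is reproduced, so d = 1.2 and 18 enrolled per group are the base for the illustration.

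**2. Where the passages lead when read together.**
- The discontinuation rule can end participation, with no provision for T2 or T3.
- A missing T2 value is drawn from a model fitted to people who have T2 data. Under this rule they are mainly people who met the 80% requirement and did not change lifestyle.
- The named predictors are baseline characteristics and earlier values. For a T2 outcome these carry no information on sessions completed or on why the person left.
- The imputed value therefore looks like that of a retained participant with a similar baseline.

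**3. Illustration for LHT versus CON, with arm in the imputation model.** Let w be the share of LHT withdrawn for non-adherence and r the share of the full effect that these people obtain. Both are assumed; the document gives neither. The effect in all randomised is d × [(1 − w) + w × r], while the reported effect stays near d = 1.2.

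| Withdrawn from LHT | True effect, r = 0 | True effect, r = 0.5 | Reported |
|---|---|---|---|
| 1 of 18 | 1.13 | 1.17 | about 1.2 |
| 2 of 18 | 1.07 | 1.13 | about 1.2 |
| 3 of 18 | 1.00 | 1.10 | about 1.2 |
| 5 of 18 | 0.87 | 1.03 | about 1.2 |

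For 3 of 18, w = 0.167: 1.2 × 0.833 = 1.00, and 1.2 × (0.833 + 0.083) = 1.10. The overstatement is 0.10 to 0.20 SD.

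**4. The same check with arm left out, LHT and CON only.** Take 18% withdrawn with no gain, so the true effect is 0.82 × 1.2 = 0.98.
- If both arms lose 18%, imputed values have the same mean in each arm. The estimate is 0.82 × 1.2 = 0.98, and the bias is nil.
- If only LHT loses 18%, the pooled mean of those retained is 0.984 / 1.82 = 0.54. The LHT mean becomes 0.984 + 0.18 × 0.54 = 1.08, against a true 0.98.

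**The case against.** The strongest reply has four parts.

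- **The rule is permissive, and loss of T2 and T3 data is not stated.** This is correct. Some non-adherers may stay and be measured, and early discontinuation could mean leaving the intervention only. But the section's opening sentence speaks of withdrawal from the study, and no sentence keeps these people in follow-up. The problem is a rule that permits the loss.
- **A Missing Not At Random analysis is planned for this scenario.** It is, and it counts in the plan's favour. It does not change the primary estimate, its size is not given, and in a three-arm trial the article does not say which arm is the treatment group.
- **Withdrawn people are imputed, not deleted, and home sessions are logged.** This also stands. A difference in adherence between arms can still be described. What moves is the primary effect estimate.
- **The size is unknown.** This stands in full.

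A reader might go further in three ways that the documents do not support. One is to treat the whole 18% attrition allowance as non-adherence with zero gain and quote a fixed inflation; the article does not break attrition down by cause. Another is to read the short list of imputation inputs as excluding arm and to claim a loss of power. That rests on silence in a condensed article, and step 4 shows that leaving arm out would offset the inflation, not add to it. The third is to say that the 80% threshold is harsher in one arm. If requirements meant sessions, it would be 57.6 of 72 heat-pad sessions and 28.8 of 36 HIIT sessions, the same proportion, and the article does not define requirements as sessions.

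**Conclusion.** The concern holds as a flaw in a stated rule. The protocol allows study participation to end for behaviour after randomisation, at the discretion of a team that includes unblinded staff, without securing the outcome visits. Imputation under Missing At Random from baseline and earlier values then moves the primary estimates toward an effect among adherers.

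The size cannot be fixed from the document. The 0.10 to 0.20 SD for LHT versus CON assumes that 3 of 18 LHT participants are withdrawn, that they obtain none to half of the effect, and that they are imputed like retained members of their arm. It is smaller or nil if arm is not in the imputation model. For LHT versus HIIT the direction depends on which arm loses more non-adherers. The illustration does not cover lifestyle-change withdrawals, whose outcomes could be better than average.

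Withdrawal for a new health condition that raises risk is a safety matter and is not challenged. The sample-size calculation is not in question.

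**What to change.** - **Criteria for discontinuing:** separate a decision about the intervention from the end of outcome follow-up. State that non-adherence or lifestyle change does not end follow-up, and that consenting participants are still invited to T2 (and T3 for LHT and CON) whatever is decided about their intervention. Report withdrawals by arm and reason.
- **Analysis set:** make the primary analysis all randomised participants by assigned arm, with the at-least-80%-adherent set as a sensitivity analysis.
- **Imputation:** impute within arm or with arm in the model, and include sessions completed.
- **Sensitivity analysis:** state the size of the penalty and the arm or arms to which it applies.

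The cost is mainly wording, since these visits are already planned for every participant. The change must come before withdrawals occur. The downside is that the estimate includes non-adherers and may be somewhat smaller. With all 18 per group measured, alpha 0.025 and the SD unchanged, contrast power is 88.9% at 1.2 SD, 82.5% at 1.10 SD and 74.1% at 1.00 SD, against 81.5% for 15 per group at 1.2 SD.

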#### Retention.

In addition to compensation, participant retention and complete follow-up are supported through multiple strategies. The anticipated time commitment is clearly communicated during screening, and participant availability is confirmed prior to enrollment. Flexible scheduling options (e.g., evenings, weekends, and rescheduling windows) are employed, along with structured engagement and retention strategies, including regular reminders, check-ins, and timely follow-up after missed visits. Adherence and patterns of missing data are monitored throughout the study to allow early identification of barriers and implementation of corrective measures (e.g., adjustment of visit timing or tailored reminders). Lastly, outcome measures, such as body composition, HbA1c, functional performance, and exercise capacity, etc., are provided at each major assessment point. An accompanying information sheet outlines the importance of these non-diagnostic results in relation to overall health (e.g., glucose regulation, body composition, fall risk). Study staff also review and explain the results to participants to ensure understanding. Collectively, these approaches are intended to optimize completion rates while preserving protocol integrity.

### Assessment of outcomes

#### Assessment of glycemic control.

Blood samples collected during the OGTT (before and 30, 60, and 120 minutes after consuming 75 g glucose) at T1, T2, and T3 will be analyzed for glucose, insulin, and C-peptide concentrations to assess glycemic control. Glucose concentrations will be measured using a GL5 Analyzer (Analox Instruments, UK) and insulin and C-peptide levels will be quantified using commercially available ELISA kits. Resulting values will be used to calculate fasting glucose (pre-OGTT) [53], glucose tolerance (1- hour and 2-hour glucose and glucose area under the curve [AUC] during OGTT) [53–55], insulin sensitivity (fasting insulin [56], insulin AUC [53], and the Quantitative Insulin Sensitivity Check Index [QISCI] [57]), insulin resistance (homeostatic model assessment of insulin resistance [HOMA-IR]), and beta-cell function (homeostatic model assessment of beta-cell function [HOMA-β] [58], C-Peptide Index [59], and Insulinogenic Index [59]).

#### Assessment of frailty risk.

Frailty risk will be assessed at T1, T2, and T3 using the Frailty Phenotype Score [1]. Frailty risk (robust, pre-frail, frail) will be determined based on gait speed (timed up and go [60]), SKM strength (handgrip dynamometry [1], complemented by 30-s sit-to-stand test [61]), unintentional weight loss (self-report, ≥ 10 lbs or ≥5% of body mass in past year [1] or between major study timepoints, assessed during questionnaires), fatigue (SF-36 energy subscale [60]), and physical activity (IPAQ [36]). These measures will be complemented by exercise capacity (VO_2peak_) testing and body composition (DEXA, anthropometric measures) since fat-free body mass is associated with lower frailty risk [49].

#### Assessment of muscle architecture.

**Muscle fiber CSA and capillarization:** Immunohistochemistry (IHC) will be used to analyze type I and type II CSA and capillary density. Muscle samples in Z-fix will be paraffin embedded, sectioned at ~5 um using a microtome, and two sections from the same sample mounted on each slide for analysis in duplicate. Samples will be prepared and immunofluorescence (IF) or immunohistochemistry (IHC) performed using previously published methods [62–64]. Briefly, after deparaffinization and epitope retrieval, sections will be blocked, and primary antibodies added followed by appropriate fluorophore-conjugated secondary antibodies. Slides will be mounted using media containing DAPI (Vectashield, Vector Laboratories, Newark, CA, USA) and imaged using widefield fluorescence (IF) or brightfield (IHC) microscopy (Cytation C10, Agilent Technologies, Santa Clara, CA, USA). Stains will include type I and type II fiber stains to assess fiber type, laminin to delineate muscle fiber borders and accurately assess CSA, and CD31 (platelet endothelial cell adhesion molecule-1; PECAM-1) to assess capillarization. CFPE will be calculated based on the proportion of muscle fibers bordered by capillaries. Images will be analyzed using ImageJ.

**Mitochondrial morphology and functional indices:** Transmission electron microscopy (TEM) will be used to analyze mitochondrial content and morphology in glutaraldehyde-paraformaldehyde-fixed muscle samples using previously published methods [65] with slight modification. Briefly, fixed samples will be rinsed, cut into small (~1 × 2 mm) segments, and post-fixed in 1% OsO_4_. Samples will then be dehydrated, embedded in epoxy resin, and sliced into ultrathin sections (~60 nm) before imaging on a Hitachi H-8100 Scanning/Transmission Electron Microscope (STEM).

As an additional index of mitochondrial content, mitochondrial DNA (mtDNA; *DLOOP*:*B2M*) will be measured using qPCR [66]. DNA will be extracted from a small portion (~10 mg) of flash frozen SKM using a commercially available DNA extraction kit (DNeasy, Qiagen) and quantified (NanoDrop, ThermoFisher Scientific, Waltham, MA, USA). Previously validated [67] custom primers designed to span exon-exon junctions will be purchased (Integrated DNA Technologies, Coralville, IA, USA). Final reactions will contain gDNA (25 ng), primers (500 mM), SyBr green (Qiagen, Venlo, Netherlands), and nuclease-free water to 20 ul. All samples from a single participant will be analyzed on the same PCR plate and reactions will be run in triplicate.

Succinate dehydrogenase (SDH) activity will be measured using histochemistry in OCT-fixed samples according to previously published methods [67]. Briefly, samples will be cross-sectioned and incubated with phosphate buffer containing sodium succinate and nitro blue tetrazolium (NBT), washed with acetone and distilled water, and mounted. Images will be acquired using brightfield microscopy (Cytation C10) and analyzed using ImageJ and custom Python code that we will make available on GitHub.

Western blotting [39,40,68] will be used to detect the concentration of electron chain complexes in flash frozen SKM samples. Proteins will be separated using SDS-PAGE, electrophoretically transferred to a low-fluorescence PVDF membrane, and total protein imaged using a ChemiDoc MP (Bio-Rad Laboratories, Hercules, CA, USA). The membrane will be blocked and incubated overnight with commercially available primary antibodies against selected proteins in each electron transport chain complex (Total OXPHOS Human Antibody Cocktail, Abcam, UK) among other mitochondrial proteins. To provide insight into potential mechanism, primary antibodies against p-TRPV1 and TRPV1 will also be applied. Membranes will then be rinsed, incubated with the appropriate secondary antibodies, and imaged using enhanced chemiluminescence on a ChemiDoc MP (Bio-Rad Laboratories). Band density will be determined using Bio-Rad image analysis software and normalized to β actin.

Citrate synthase activity [69] will be measured in lysed flash frozen skeletal muscle samples in duplicate using a commercially available enzymatic assay (CS0720, Sigma-Aldrich, Burlington, MA, USA) and spectrophotometry.

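### The trial is powered on the capillary-fiber perimeter exchange index, but the calculation given for it is a share of fibers with no perimeter term, so d = 1.2 has no stated basis for what will be measured

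*Protocol article*

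**What the plan says.** The Power analysis section names the variable that sets the sample size: "Because capillary-fiber perimeter exchange index (CFPE) is a widely measured variable and an important component of anticipated adaptations", the results of a cited local heat therapy (LHT) study were used. Of that study it reports: "They observed significantly greater CFPE with LHT vs CON (d > 1.5"). The planning value follows: "We used a more conservative, d = 1.2 (reduced by 20%), because older adults might have a blunted response to LHT". All the power figures rest on it:

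- the three-group ANOVA ("f = 0.4899, α = 0.05) will require 45 total participants (15 per group) to achieve 80% power");
- the two planned contrasts ("d = 1.2, α = 0.05/2 [Bonferroni"]), also with 15 per group;
- the Aim 2 comparison ("d = 1.2, a = 0.05, 15 participants per group) will achieve 89% power").

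The section on assessment of muscle architecture is the only place that says how CFPE will be obtained: "CFPE will be calculated based on the proportion of muscle fibers bordered by capillaries". The same paragraph plans stains for fiber type and "laminin to delineate muscle fiber borders and accurately assess CSA, and CD31" for capillaries. Fiber borders are mentioned there for cross-sectional area (CSA); no perimeter measurement is described. The Introduction lists capillary density and CFPE as separate measures.

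**The concern.** By its name, a capillary-fiber perimeter exchange index relates capillary supply to fiber perimeter. A share of fibers that have a capillary at their edge is another kind of quantity. It has no perimeter in it, it stops at 100%, and on a literal reading a fiber moving from three adjacent capillaries to five scores no change.

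The effect size was observed on the index. If image analysts score the share, the trial measures one quantity and is powered on another. A real gain in capillary supply could then be partly or largely missed, and the results could not be set beside those of the sizing study. Capillary density, the other capillary measure named, does not fill the gap: it falls when fibers grow unless capillaries rise as well, and the Introduction expects heat therapy to increase fiber area.

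**Working it through.** **1. Inputs from the Power analysis.** d = 1.5 × 0.8 = 1.2; three groups; 15 per group; α = 0.05 for the ANOVA and for Aim 2; α = 0.05/2 = 0.025 for each contrast. Sidedness is not stated; two-sided tests reproduce the figures.

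**2. The plan's own figures.**

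- ANOVA: f = d/√6 = 1.2/2.449 = 0.4899 (third mean midway between the other two). Noncentrality f²N = 0.24 × 45 = 10.8. Power from the noncentral F is 0.817; with N = 42 it is 0.786. So 45 is the smallest balanced total for 80%.
- Contrast: noncentrality d√(n/2) = 1.2 × √7.5 = 3.29 on 28 df, α = 0.025. Power is 0.815; with 14 per group it is 0.782.
- Aim 2: the same noncentrality at α = 0.05 gives 0.887, the stated 89%.

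All three reproduce. The arithmetic is not at issue.

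**3. The two descriptions side by side.**

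| | Power analysis | Muscle architecture section |
|---|---|---|
| Quantity | Exchange index per fiber perimeter | Share of fibers with a capillary at the border |
| Perimeter enters | Yes, by name | No |
| Upper bound | None implied | 100% |
| Effect size given | d > 1.5, planned as 1.2 | None |

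The two also react differently to fiber growth. If CSA rises by 10%, perimeter rises by about √1.1, so a per-perimeter index changes by a factor 1/√1.1 = 0.953 with the same capillaries. The share does not change by construction.

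**4. What a smaller d would do.** Power of one contrast, 15 per group, two-sided α = 0.025:

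| d on the measured variable | 1.2 | 1.0 | 0.8 | 0.6 | 0.4 | 0.2 |
|---|---|---|---|---|---|---|
| Power | 81% | 65% | 44% | 25% | 12% | 5% |

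**5. How much of d could survive on the share.** The document gives no capillary counts, so everything in this step and the next is assumption. If contacts per fiber are Poisson with mean m, the share is 1 − exp(−m). A 20% rise in m then moves it from 86.5% to 90.9% (m = 2), 95.0% to 97.3% (m = 3), 98.2% to 99.2% (m = 4) or 99.3% to 99.8% (m = 5).

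A simulation used Poisson or bounded-binomial contacts, a between-person CV of 20%, an SD of change of 15% of the mean, 50 to 200 fibers per biopsy, and d = 1.2 in each person's true mean contacts:

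| Assumed baseline share | d on the share | Contrast power |
|---|---|---|
| 0.50–0.80 | about 0.5–0.9 | about 20–54% |
| 0.91–0.94 | about 0.5–0.8 | about 19–42% |
| 0.96–0.98 | about 0.4–0.6 | about 8–28% |
| 0.995 | about 0.3 | about 4–7% |

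**6. A fairer calibration.** The d in the Power analysis is an observed effect, so it already contains fiber-sampling noise; step 5 adds that noise a second time. Setting the observed d in contact counts to 1.2 instead raises the power of the share at m = 2 to about 45% (100 fibers) or 57% (200 fibers). It hardly changes the results at m = 4 to 5.

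At a low baseline share the loss becomes small. Take m = 0.7 (share 0.50), 200 fibers and SD of change 0.15 × 0.7 = 0.105:

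- Shift needed for observed d = 1.2 in counts: 1.2 × √(0.105² + 2 × 0.7/200) = 1.2 × √0.01803 = 0.161.
- Slope of the share: exp(−0.7) = 0.497, so the share moves by about 0.497 × 0.161 = 0.080.
- SD of change in the share: √[(0.497 × 0.105)² + 2 × 0.503 × 0.497/200] = √(0.00272 + 0.00250) = 0.072.
- d on the share: 0.080/0.072 = 1.1, so power lies between the 65% and 81% of step 4.

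This is a first-order figure. It slightly overstates d, because the curve flattens as m rises.

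**The case against.** The strongest reply is that this is one condensed sentence in an article. It says the calculation is based on the share, which is softer than a definition, and no yes/no scoring rule is written. The staining methods around it are summarized with references, a manual of procedures exists, and laminin with CD31 would support a full per-fiber perimeter calculation. The investigators may well intend the proper index.

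That may be so, and it limits how firmly one can say that capillaries after the first are ignored. It does not remove the point. The article does not leave the formula to another document; it states a basis for the calculation, and that basis does not match the named index. If it is loose shorthand, it still needs correcting, because an analyst following it would score another quantity.

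A reader might go further and infer that the share sits near its ceiling, so that the assumed effect cannot appear. The document does not support this. It gives no baseline share, mean, SD or capillary count, and the high shares in step 5 come from assumed means. In every scenario the effect shrinks but does not vanish.

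Nor does the fiber-growth argument show harm in one direction: growth alone would lower a per-perimeter index and leave the share where it was. It shows only that the two are different quantities. Finally, CFPE is the variable used for sizing, but the document does not single it out as the one primary endpoint.

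**Conclusion.** The point holds as a mismatch between two sections. The Power analysis relies on a perimeter-based index, and the muscle architecture section describes a bounded share without perimeter. For that share, d = 1.2 and the stated power have no stated basis.

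The consequence cannot be given as one figure. Under the assumptions shown, d on the share runs from about 1.1 (low baseline share, many fibers, observed d calibrated to 1.2) to about 0.3 (share near 0.995). Contrast power then runs from somewhat below the planned level to under 10%. The direction is consistent; the size depends on a baseline and a fiber number that the document does not give. If CFPE is measured as named and in the same way as in the sizing study, the sample size calculation stands.

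**What to change.** Replace the CFPE sentence in the muscle architecture section with a calculation of capillary supply per fiber relative to fiber perimeter, and state that the formula is the one used in the study that supplied the effect size. The exact formula is not in the document and should be taken from that study. Fix it before images are scored, so that the choice of definition cannot depend on the results. Drop the share of bordered fibers, or report it under its own name.

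If the share is to remain as CFPE, give an effect size and SD for it with their source, state the number of fibers to be scored per biopsy, and restate the power.

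The cost is small. The laminin, CD31 and fiber-type images are already planned; one sentence and the image measurement change, with somewhat more analysis time per biopsy. With CFPE measured as named, 15 per group (45 analyzed, 54 enrolled) is unchanged.
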